### Intervention Group

In addition to receiving iron capsules, which are standard supplements provided by the health centers as part of the national prenatal care program, participants in the intervention group also received *M. oleifera* extract supplementation at a dose of 2000 mg/day, administered as 2 capsules taken twice daily (totaling 2000 mg/day) for a continuous period of 8 weeks. Supplementation began immediately upon enrollment, which occurred between gestational weeks 20 and 32. Therefore, the regimen lasted from the time of enrollment until 8 weeks later, typically ending between weeks 28 and 40 of gestation. For participants enrolled in the late third trimester who delivered before completing the full 8 weeks, they were instructed to continue consuming the remaining *M. oleifera* supplements until the full course was completed. This approach aimed to ensure consistency in the intervention dosage, regardless of the timing of delivery, and to maintain the study’s internal validity.

To support adherence, we collaborated with health cadres at each participating health center. The cadres will be responsible for supervising, reminding, and ensuring that the mothers consistently take the moringa capsules. A WhatsApp group was established specifically for the cadres to facilitate regular communication, provide reminders, and monitor the supervision process throughout the 8-week supplementation period. We have also added a simple adherence log that will be maintained by the cadres, documenting capsule intake daily based on direct questioning or observation. These dual approaches—cadre monitoring and pill counts—will allow us to triangulate adherence data and better distinguish true intervention effects from variability due to compliance.

Participants will be actively monitored for adverse events throughout the 8-week intervention period. At the follow-up visit, participants will be asked about any symptoms or side effects experienced, using a structured checklist and open-ended questions. Specific adverse events of interest include gastrointestinal discomfort (nausea, vomiting, and diarrhea), allergic reactions (skin rash and swelling), and general intolerance to the supplement.

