Any serious adverse events, including pregnancy complications such as preeclampsia, gestational diabetes, preterm labor, or hospitalizations, will be recorded and reviewed by the study physician. Although these are not primary outcomes, maternal and fetal complications will be documented to ensure a complete safety profile.

Prior evidence suggests that *M. oleifera* supplementation at a dose of 2000 mg/day is safe for human use, including during pregnancy. However, all safety data will be recorded in participant case report forms, monitored by the study team, and summarized in the final report.

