### Control Group

Mothers in the control group will receive only the standard iron supplement. Although iron itself may influence oxidative stress, this effect can be controlled by equalizing iron intake across groups. They will be counseled on dietary sources of antioxidants and offered *M. oleifera* supplementation after study completion if desired. This delayed intervention strategy has been approved by the local ethics committee and was explained during informed consent.

To minimize the risk of measurement and performance bias, participants in the control group were not informed about the specific intervention given to the other group.

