#### Safety and Tolerability of *M. oleifera*

Hypothesis: *M. oleifera* supplementation will be safe for pregnant women, with no significant adverse effects reported during the intervention period. Hence, the expected results are as follows: (1) Minimal to no adverse effects in the group receiving *M. oleifera* supplementation. (2) This safety profile is consistent with previous studies indicating that 2000 mg/day is safe for pregnant women.

This will provide further evidence that *M. oleifera* is a safe supplement for pregnant women, supporting its use in future clinical applications and maternal health programs.

In the final analysis, changes in heavy metal levels (Pb, Cd, and Hg) will be reported individually, as well as in aggregate if appropriate. Similarly, biomarkers of oxidative stress (8-OHdG and MDA) will be analyzed and reported separately. While the study is not powered for definitive subgroup comparisons, exploratory reporting by relevant characteristics (eg, trimester, nutritional status, and baseline exposure level) will be presented to generate hypotheses for future studies.

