## Discussion

### Principal Anticipated Findings

This study is expected to demonstrate that *M. oleifera* supplementation during pregnancy reduces blood levels of heavy metals and decreases oxidative stress biomarkers (8-OHdG and MDA). It also aims to confirm the safety and tolerability of moringa in pregnant women, laying the groundwork for its use as a low-cost, locally available intervention for mitigating environmental pollutant-related health risks.

Several animal studies have shown that moringa leaf extracts can significantly reduce heavy metal accumulation in vital organs and mitigate oxidative stress caused by Pb, Cd, and Hg exposure. These effects are attributed to its high content of flavonoids, phenolic acids, glucosinolates, and carotenoids, which act as free radical scavengers and binders of toxic metals.

While direct clinical evidence in pregnant women remains limited, moringa has been used traditionally in many parts of Indonesia and other countries as a nutritional supplement and natural remedy, including during pregnancy. Small-scale human studies in nonpregnant populations have reported improvements in antioxidant status and reductions in lipid peroxidation following moringa supplementation. This study assumes that the biological mechanisms observed in preclinical research—namely, antioxidant protection and chelation of toxic metals—will translate to similar detoxifying effects in pregnant women.

Importantly, while this study does not evaluate direct clinical outcomes (eg, birth weight, gestational age), the primary focus is on biomarker-based improvements, which are commonly used as surrogate indicators of fetal and maternal risk. The findings are expected to strengthen the biological plausibility for moringa as a preventive intervention in polluted environments and inform the design of future clinical outcome studies.

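### Adverse-event collection is described only for the supplemented women, yet the article aims to confirm safety, which neither a one-arm count nor 26 to 59 exposed women can do

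*Protocol article*

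**What the plan says.** The safety procedures are in Methods, Intervention Group. That section states: "Participants will be actively monitored for adverse events throughout the 8-week intervention period". It then gives the step by which symptoms are elicited: "At the follow-up visit, participants will be asked about any symptoms or side effects experienced", using a fixed checklist together with open questions. The events of interest are gastrointestinal discomfort, allergic reactions and "general intolerance to the supplement". Serious events, with preeclampsia, gestational diabetes, preterm labor and hospitalization named, are to be recorded and reviewed by the study physician, and "maternal and fetal complications will be documented to ensure a complete safety profile".

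The Control Group section begins "Mothers in the control group will receive only the standard iron supplement". It goes on to dietary counseling, a later offer of moringa, and keeping the nature of the intervention from these women. It describes no adverse-event collection. Participant Recruitment gives controls a follow-up blood draw after two months, at an antenatal visit. Data Collection lists metals, 8-OHdG and MDA as the outcomes measured at both time points.

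On the safety claim, the Safety and Tolerability section hypothesizes that the supplement will be safe, "with no significant adverse effects reported during the intervention period", and expects "Minimal to no adverse effects in the group receiving" moringa. It gives no comparator, rate or margin. Principal Anticipated Findings says of the study: "It also aims to confirm the safety and tolerability of moringa in pregnant women". The section on blood heavy metal levels expects the result to show a safe and effective approach. Against this, the Abstract's Conclusions promise preliminary evidence on safety. Later in Principal Anticipated Findings the results are called hypothesis-generating, and Strengths and Limitations and the Conclusion also call them preliminary.

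**The concern.** Two things do not fit together. First, the expected safety result concerns one arm, while the named complications are not specific to the supplement. The Introduction itself links preeclampsia and preterm birth to oxidative stress from metal exposure, and eligibility requires elevated metals in both arms. Both arms also take iron. If events are known only for supplemented women, a few cases of preterm labor could be dismissed as background or blamed on moringa, and the data could not settle which.

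Second, confirming safety is a stronger claim than the design allows. An absence of reported events in a few dozen women still leaves room for sizeable risks. The article expects the safety result to support use in maternal health programs, and the Dissemination Plan intends to bring the findings into such programs, so the claim may be acted on in pregnant women.

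**Working it through.** **No safety figure to reproduce.** The only sample size calculation (Participant Recruitment: 37 per group, 44 after dropout) is for 8-OHdG. No adverse-event rate, margin or precision target is stated.

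**Inputs from the article.** Exposed women: 26 (Results, Overview: 26 per group have participated), 44 (sample size text) or 59 (recruitment text). These three figures disagree, so all are carried through.

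**Step 1: what zero events would exclude.** If none of n women has an event, the exact upper bound on the true rate is U = 1 − α^(1/n), with α = 0.05 for a one-sided 95% bound and 0.025 for the upper end of a two-sided 95% interval.

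| n | one-sided: 1 − 0.05^(1/n) | two-sided: 1 − 0.025^(1/n) |
|---|---|---|
| 26 | 10.9% | 13.2% |
| 44 | 6.6% | 8.0% |
| 59 | 5.0% | 6.1% |

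**Step 2: chance of seeing no event at all.** This is (1 − p)^n. The true risks p are assumptions.

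| p | n = 26 | n = 44 | n = 59 |
|---|---|---|---|
| 5% | 26% | 10% | 5% |
| 2% | 59% | 41% | 30% |
| 1% | 77% | 64% | 55% |

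**Step 3: what control data would add.** The event rates here are also assumptions, because the article gives none.

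- With a true rate of 10% in both arms, the approximate 95% half-width for the risk difference is 1.96 × √(2 × 0.10 × 0.90 / n). That is 16.3 percentage points at n = 26, 12.5 at n = 44 and 10.8 at n = 59.
- At 26 per arm and two-sided 5%, power for 10% versus 20% is 17% by the normal approximation and 9% by Fisher's exact test. For 10% versus 30% it is 44% and 32%.
- At 59 per arm the normal approximation gives 33% and 78% for the same two contrasts.
- Power of 80% for 10% versus 20% needs about 199 per arm.

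**Reading the results together.** Without controls, no excess risk can be estimated at all. With controls, it can be estimated without a built-in gap, but only imprecisely. Collecting control events is therefore needed for a comparison, yet would not by itself justify the word confirm. The wording has to change as well.

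**The case against.** The strongest objection is that the one-arm reading rests on the placement of text under a heading. The monitoring sentence says participants without naming an arm, although the same section names the intervention group when it means that arm. The serious-event text is equally general. A condensed article may leave control-arm forms to the full protocol. This stands to the extent that a reader might infer that controls are not monitored, and the article does not say so. What it supports is narrower: collection is described only under the intervention group, over the intervention period, with one item that can apply only to supplement users, and the expected result is stated for that group alone.

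A reader might also infer that monitoring comes down to one recall question. The text does not support that. It specifies a structured checklist with open questions, recording of serious events, physician review and case report forms. It is fair to say only that the one symptom inquiry described takes place at the follow-up visit.

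Nor is a one-arm count worthless. Review of individual serious events and a plain description of tolerability are informative without controls. They cannot give an excess risk.

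Finally, safety is absent from the Objective and from the primary and secondary outcomes in the Abstract, and several sections call the findings preliminary. That is correct and keeps the point in proportion. It does not remove the conflict, because safety has its own hypothesis and the claim to confirm it appears in the same section as the hypothesis-generating caveat.

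**Conclusion.** The point holds in this limited form. As described, the study collects adverse events in the supplemented arm only and sets out to confirm safety, in conflict with its own preliminary wording. Counts from one arm cannot show whether pregnancy complications are more frequent with moringa. Zero events would leave true rates up to 10.9%, 6.6% or 5.0% open at 26, 44 or 59 exposed women (one-sided 95%), so the conclusion does not depend on which of the article's sample sizes applies.

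Those bounds assume complete ascertainment and independent women, and need no assumed event rate. The missed-event probabilities and power figures do rest on assumed rates and are illustrative. Whether the full protocol collects events in controls cannot be told from the article. If it does, the remaining fault is the wording of the safety claim and the lack of a stated comparison.

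**What to change.** - **Collection.** Apply the same symptom checklist, without the supplement-intolerance item, and the same serious-event recording to controls at their existing two-month visit, and say so in the Control Group section.
- **Visits already past.** With 26 women per group already reported and second-step laboratory work under way, some visits may be over. Take complications from antenatal records for those women, using the same source in both arms. Records may not capture minor symptoms. Where controls were not asked, describe symptoms in the supplemented arm only and state that no comparison is possible.
- **Equal ascertainment.** Do not add a symptom line to the cadres' capsule log. That log exists only in the intervention arm, and in an unblinded study more intensive questioning of one arm would bias the difference.
- **Reporting.** Give counts by arm and the between-arm difference with exact confidence intervals, as estimates rather than a test of safety.
- **Wording.** In the heavy-metal expected outcomes, Safety and Tolerability, and Principal Anticipated Findings, replace the claims to confirm or demonstrate safety with an aim to describe tolerability, in line with the preliminary wording elsewhere.

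The cost is one extra form at a visit that already takes place, some record review where visits have passed, and a softer safety claim. The supplement regimen and clinical care are unaffected.

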### Participant Recruitment

This research has been conducted in Makassar City, specifically at 6 community health centers where expectant women receive prenatal services. The 6 selected community health centers are located in areas with varying environmental characteristics, including industrial zones, regions near landfill sites, and coastal areas. While the types of pollution sources differ, all sites share a common feature: exposure to potential environmental contaminants. Each represents an urban setting with a plausible risk of heavy metal exposure through air, water, and food pathways. Thus, despite differences in specific pollution types, the study sites are considered comparable in terms of overall environmental risk exposure. This selection strategy ensures that the intervention and control groups are drawn from communities facing similar environmental health challenges. Moreover, such variation may enhance the generalizability of findings across different urban pollution contexts. Three centers were assigned as intervention sites and 3 as control sites based on operational convenience and to avoid information spillover between groups.

The study will include 59 pregnant women in each group of intervention and control who underwent an examination at health centers in Makassar and fulfilled the following inclusion criteria: (1) pregnancy during the second or third trimester, (2) intention to deliver in Makassar, (3) living in Makassar for a period exceeding 1 year, and (4) blood levels of Hg, Pb, or Cd exceeding the reference value. Participants will be excluded based on self-report during interview if they (1) are having twin pregnancy, (2) had known chronic medical conditions, such as diabetes, cancer, kidney diseases, (3) are taking other antioxidant or mineral supplements beyond standard care, (4) are diagnosed with micronutrient deficiencies, (5) relocate during the intervention period, and (6) are unwilling to comply with follow-up procedures.

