The required sample size was calculated using an estimated effect size (Cohen *d*) of 0.42, derived from a previous intervention study in South Sulawesi, which assessed the effects of *M. oleifera* supplementation on oxidative stress biomarkers in pregnant women exposed to passive smoking [37]. The study reported a mean difference in 8-OHdG levels between treatment groups of approximately 12.96 ng/mL with a pooled SD of ~30.68 ng/mL, yielding a moderate effect size. Using a 1-sided test with *α*=.05 and 80% power, the minimum required sample size is 37 participants per group. To account for an anticipated 20% dropout rate, the sample size was increased to 44 participants per group, yielding a total of 88 participants.

Approximately 200 pregnant women attending routine antenatal care (ANC) visits at the community health centers were sequentially approached and invited to participate in the study. They were first interviewed to determine eligibility based on inclusion and exclusion criteria. Those meeting the criteria were provided with detailed information about the study and asked to provide written informed consent. Following consent, a blood sample was collected to assess baseline levels of heavy metals.

Only participants with elevated levels above reference thresholds were considered eligible for inclusion in the intervention phase. For the intervention group, eligible participants were contacted and provided with *M. oleifera* supplements along with instructions for daily consumption over a 2-month period. They were informed that a follow-up blood collection would occur at the end of the supplementation period during a routine visit.

For comparison, the control group was recruited from a different health center in a separate subdistrict administrative unit that did not receive moringa supplementation. This approach minimized contamination between groups and allowed for feasible implementation of the intervention. Follow-up blood sampling was also conducted after 2 months, aligned with their next scheduled antenatal visit, but without providing moringa supplementation.

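### The planned safety conclusion rests on symptoms in the moringa group alone, with no control-group enquiry described to compare them with

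*Protocol article*

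**What the plan says.** The adverse-event text stands in the Methods under Intervention Group. It opens with a general commitment: "Participants will be actively monitored for adverse events throughout the 8-week intervention period". It then describes one instrument for symptoms: "At the follow-up visit, participants will be asked about any symptoms or side effects experienced, using a structured checklist and open-ended questions". The events of interest named there are gastrointestinal discomfort (nausea, vomiting, diarrhea), allergic reactions (rash, swelling) and general intolerance. Serious events and pregnancy complications are to be recorded and reviewed by the study physician.

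Participant Recruitment tells the intervention group that "a follow-up blood collection would occur at the end of the supplementation period during a routine visit". Enrollment is at gestational weeks 20 to 32, so supplementation runs for 8 weeks, "typically ending between weeks 28 and 40 of gestation".

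The Control Group section describes standard iron, dietary counselling and an offer of moringa after the study. It describes no symptom enquiry. Controls do have a suitable contact, though: "Follow-up blood sampling was also conducted after 2 months, aligned with their next scheduled antenatal visit, but without providing moringa supplementation".

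The section Safety and Tolerability, under Expected Outcomes, states a safety hypothesis and an expected result of few or no adverse effects, judged in the treated group. It says this will be further evidence that moringa is safe in pregnancy and will back its use in later clinical applications and maternal health programs.

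**The concern.** Safety is a stated hypothesis with a stated conclusion, and the conclusion is meant to reach public health programs. The evidence described for it is a symptom count in one arm. Several listed symptoms, such as nausea, vomiting and swelling, are also ordinary complaints of late pregnancy, which is when the follow-up visit falls.

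Without the same questions put to controls, a high count cannot be blamed on the capsule. A low count has no background rate to be set against, and in a group this small it excludes only fairly common events. At stake is whether the final report can say anything about tolerability beyond listing what treated women mentioned.

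**Working it through.** The document gives no adverse-event rate, safety sample size or safety power, so there is no stated figure to reproduce. The check sets the texts side by side and then puts a scale on the conclusion.

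**Inputs**
- Women per group: 26 have participated (Results, Overview). The sample-size paragraph of Participant Recruitment says "the sample size was increased to 44 participants per group", and the same section also says "The study will include 59 pregnant women in each group". All three numbers are carried, with 26 as the main case.
- Timing of the follow-up visit: weeks 20 to 32, plus 8, gives weeks 28 to 40. Women who deliver before finishing their capsules are asked after delivery.
- Background rate b, the share of women with a listed complaint at that stage regardless of moringa: the documents give none. Assumed range 10% to 50%.

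**1. What zero events would show.** The exact one-sided 95% upper limit for 0 of n is 1 − 0.05^(1/n).
- n = 26: 1 − 0.05^(1/26) = 10.9%
- n = 44: 1 − 0.05^(1/44) = 6.6%
- n = 59: 1 − 0.05^(1/59) = 5.0%

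These limits assume that every event is captured. They reflect sample size, not the way symptoms are asked.

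**2. What a non-zero count would show.** The expected number of treated women with a complaint, if the capsule does nothing, is 26 × b.
- b = 10%: 2.6 women
- b = 30%: 7.8 women
- b = 50%: 13 women

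Over the assumed range, an inert capsule would therefore produce anything from about 3 to 13 reports. Any observed count in that range fits no effect, and nothing in the one-arm data says which b applies.

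**3. What control data would add.** With the same items asked of 26 controls, the approximate 95% half-width of the difference in proportions is 1.96 × √(2b(1 − b)/26).
- b = 10%: 1.96 × √(0.18/26) = 16.3 percentage points
- b = 30%: 1.96 × √(0.42/26) = 24.9 points
- b = 50%: 1.96 × √(0.50/26) = 27.2 points

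Control data would supply the missing background rate and a difference with an interval, but a wide one. At 59 per group the half-width is still 1.96 × √(0.18/59) = 10.8 points for b = 10% and 1.96 × √(0.50/59) = 18.0 points for b = 50%. These half-widths ignore clustering by health center.

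**The case against.** **The claim is already tempered.** The abstract's conclusion, the Discussion, the limitations and the final Conclusion call the findings preliminary, exploratory or hypothesis-generating, and the abstract applies this to safety by name. Safety is neither the primary nor a secondary outcome. All of that stands and keeps the point minor. It does not correct the sentence in Safety and Tolerability, which still moves from a treated-group result to support for programs. The listed limitations do not mention the lack of comparator safety data.

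**The article is condensed.** A control-group symptom form may be in the full protocol. That is possible, and if so, saying so settles the collection part. The safety hypothesis and expected result as printed are nevertheless framed on the treated group.

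**A stronger reading is tempting.** A reader might infer that the commitment to monitor throughout the 8 weeks is contradicted by a single checklist at the end, especially as the cadres' log is described as "documenting capsule intake daily based on direct questioning or observation" and not as recording symptoms. The text does not support that. It never says that the checklist is the only enquiry, and it adds physician review of serious events and study-team monitoring of recorded safety data. Whether symptoms are also asked about during the course cannot be judged from this article. For the same reason, one should not infer that allergic signs would fail to reach the study physician, or that serious events go unrecorded in controls.

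**The gain is small.** Half-widths of 16 to 27 points allow description only. Allocation by center, and the fact that treated women know they take capsules, would also color any difference. This stands, and it is a reason to keep the comparison descriptive. It is not a reason to do without a background rate.

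**Conclusion.** The concern holds as a mismatch between the planned safety conclusion and the one-arm evidence described for it. It does not hold as a contradiction about how often symptoms are monitored.

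Followed as written, about 26 treated women would supply a count that cannot be attributed to moringa and cannot show the absence of an effect. Zero events would still be compatible with a true rate of up to 10.9% (6.6% with 44 women, 5.0% with 59).

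The verdict rests on two assumptions. The first is that no control-group symptom enquiry exists beyond what the article describes. The second is that some listed complaints occur in late pregnancy without moringa; the 10% to 50% range is illustrative. If control data are in fact collected, what remains is the wording of the conclusion, which would still go beyond what a group of this size can show. This is a minor point with a cheap remedy.

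**What to change.** The article does not say whether dosing is complete; laboratory work on the second step was under way in February 2025. The fix therefore has two branches.

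**If follow-up visits remain:** ask controls the same symptom items at their scheduled 2-month visit. Word them without naming moringa, because controls are not told what the other group receives. Report both arms side by side, descriptively, with an interval for the difference. Do not add weekly symptom questions for the intervention group alone, since that would prime its answers at week 8 and make the arms unequal.

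**If dosing is complete:** report when symptoms were asked, in which arm and of how many women. Give an exact upper confidence limit for any zero or low count (for 0 of 26, 10.9%, one-sided 95%). Limit the Safety and Tolerability statement to preliminary tolerability and remove the claim of support for maternal health programs.

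**Cost:** in the first branch, a few minutes per control visit and an amendment. In the second, reporting and wording only. The price in both is a weaker safety statement, and the between-arm comparison stays imprecise.
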